#### Biomarkers associated with disease recurrence and physiological health status

##### Blood sampling

Blood samples will be drawn from an antecubital vein between 8:30–10 a.m. in the morning, following a 12 hour overnight fast. Blood will be collected into Vacutainer tubes (BD Biosciences Ltd, Oxford, U.K.), containing EDTA for leukocyte counts, plasma biomarker and immune function analysis. NK cells and T lymphocytes will be isolated from whole blood within 2 h of venepuncture for analysis of NK Cell and T cell function. Plasma samples will be stored at -80°C for batch-analysis at a later date. All flow cytometric analyses, leukocyte functional assays and enzyme immunoassays will be performed in the Biomedical Sciences Research Centre, Sheffield Hallam University, under the supervision of one of the key personnel, [name].

##### Estrogen, stress hormones and inflammatory markers

Plasma IL-6, epinephrine and norepinephrine levels will be measured using commercially available enzyme-linked immunoassays (ELISA) kits (Bio-Quant Inc and Immunobiological Laboratories, Hamburg, R & D Systems UK) and plasma hs-CRP will be measured by the Immunology Department, Northern General Hospital, Sheffield using a turbidimetric assay. Serum estradiol, estrone and estrone sulphate will be measured using high-sensitivity ELISA kits Bio-Quant Inc., CA, USA and Diagnostic Systems Laboratories Inc., OBI-DSL, Oxon, UK). Salivary cortisol levels will be measured on each of three consecutive days at 0800, 1200, 1700 and 2100 hours and the slope of diurnal cortisol variation will be determined from the pooled saliva samples at each daily time point using a regression of the log-transformed cortisol concentrations on sample collection time [38]. Easy-Reach Radio Pagers (British Telecommunications Plc, UK) will be used to signal saliva collection times and the importance of collecting samples at the designated times and recording the actual sample collection time will be emphasized. Saliva samples will be refrigerated, before collection within 2–4 days and frozen at -70°C until analysis[40] using a high sensitivity salivary cortisol enzyme immunoassay (Salimetrics LLC, PA, USA).

##### Differential leukocyte counts

Differential leukocyte counts and other haematological parameters will be measured within 6 hours of blood sampling in the Department of Haematology, Royal Hallamshire Hospital (CPA accredited) using a Coulter STKS automated haematological analyser (Beckman Coulter U.K. Ltd, High Wycomb, U.K.) which is calibrated on a daily basis.

##### Lymphocyte phenotyping

The proportion of NK (CD3^-^CD16^+^CD56^+^) and T cell subsets (CD3^+^CD4^+^; CD3^+^CD8^+^) will be measured using whole blood multicolour flow cytometry. Whole blood will be collected into EDTA anticoagulant and 100 μl aliquots incubated with appropriate combinations of fluorochrome (PE/FITC/PerCP)-conjugated monoclonal antibodies (mAb) to CD3, CD4, CD8, CD16 and CD56 using triple antibody sets (BD Biosciences Ltd). Lymphocyte and monocyte populations will be located on the basis of forward and side scatter and dead cells will be excluded. The proportion of cells expressing the given combination of antigens will be determined using a BD Biosciences FACSort™ flow cytometer and CELLQuest Pro™ data acquisition and analysis software. Appropriate isotype matched, negative control antibodies will be included in all analyses.

##### NK cell activity

NK cell activity will be determined as the capacity of peripheral blood mononuclear cells to kill human erythroleukemia K562 target cells using flow cytometry, essentially as described previously [101]. Briefly, K562 cells in the log phase of growth will be harvested, washed and stained with the stable membrane dye PKH2 (BD Biosciences). Human peripheral blood mononuclear cells will be isolated by density gradient centrifugation on Ficoll (Sigma UK) and monocytes/macrophages will be removed by plastic adherence (37°C, 1 h). Two-fold serial dilutions of effector cells (800 μl; starting at 10^6 ^cells/ml) will be placed in 12 × 75 mm polystyrene tubes with 100 μl PKH2 labelled target cells (10^5 ^cells) to give a range of effector to target cell ratios (80:1 to 5:1). Samples will be incubated at 37°C for 4 h after which time the DNA stain propidium iodide (which only stains non-viable cells) will be added. The proportion of PKH2^+^PI^+ ^(non-viable) K562 cells at each effector to target cell ratio will be determined after 15 min by flow cytometry. Appropriate controls (effector cells only; target cells only) will be included in all experiments.

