Regular physical activity can also have a positive effect on psychological health status [71,72] and quality of life [73] in breast cancer survivors that could enhance immune function through normalisation of stress hormone levels. Although there is evidence for decreased cortisol levels [74,75] and changes in immune cell numbers and function after psychosocial interventions in breast cancer patients [76,77], only three studies have investigated the effects of exercise therapy on immune function in breast cancer survivors. Peters *et al*. [78,79] reported an increase in the percentage of NK cells and an improvement in NK cell function and monocyte phagocytic capacity that was accompanied by an increase in 'satisfaction of life' score after seven months of moderate exercise training, whereas Nieman *et al*. [80] did not observe any change in NK cell function following a shorter period of training. The latter study had only six subjects in the experimental (exercise therapy) group, and neither study measured stress hormone levels in patients. In a more recent study, Fairey *et al*. [81] showed that a 15 week programme of aerobic exercise training improved NK cell cytotoxic activity and peripheral blood lymphocyte function in postmenopausal breast cancer survivors. In sedentary, healthy individuals, regular moderate aerobic exercise has been shown to boost NK cell function [82] and decrease the incidence of upper respiratory tract infections in previously sedentary individuals [82-84]. In elderly females however, evidence for an improvement in immune cell function with aerobic exercise training is inconclusive, although highly trained elderly females exhibit superior resting NK cell function and T cell proliferation responses compared to age-matched sedentary controls [83]. The lack of intervention studies incorporating biomarkers of immune function in women recovering from breast cancer treatment is surprising, as restoration of lymphocyte and NK cell function after treatment is predictive of survival [28,85,86] and is independent of stage of disease and adjunctive treatment approach [86]. This suggests that lifestyle interventions which could have an impact on immune function are worth exploring, as they could have a significant influence on disease-free survival in breast cancer patients.

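### NK cell activity is scaled to all non-adherent mononuclear cells, so a shift in NK proportion can look like a change in NK cell function; a per-NK-cell analysis alongside would separate the two

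*Protocol article*

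**What the plan says.** The section NK cell activity defines the outcome: "NK cell activity will be determined as the capacity of peripheral blood mononuclear cells to kill human erythroleukemia K562 target cells". The cells are separated on Ficoll, and then "monocytes/macrophages will be removed by plastic adherence (37°C, 1 h"). No step that purifies NK cells follows. The tubes are set up as "Two-fold serial dilutions of effector cells (800 μl; starting at 10^6 ^cells/ml") with "100 μl PKH2 labelled target cells (10^5 ^cells"), which is said "to give a range of effector to target cell ratios (80:1 to 5:1"). The readout is the proportion of dead target cells at each ratio.

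The section Blood sampling describes the cells differently: "NK cells and T lymphocytes will be isolated from whole blood within 2 h of venepuncture for analysis of NK Cell and T cell function".

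The section Lymphocyte phenotyping collects the NK proportion (CD3-, CD16+, CD56+) in the same sentence that says the "T cell subsets (CD3^+^CD4^+^; CD3^+^CD8^+^) will be measured using whole blood multicolour flow cytometry".

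The last paragraph of the Background hypothesises about NK cell function as an index of immune function. Earlier, the Background cites an exercise study in breast cancer survivors that found "an increase in the percentage of NK cells and an improvement in NK cell function", so it lists the two as distinct results. Data Analysis applies a mixed factorial ANOVA to all outcome measures and Pearson correlations to changes. It states no scaling of the killing assay by NK proportion.

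**The concern.** If NK cells do the killing, which calling the assay NK activity presupposes, then the ratio that matters is NK cells to targets. The plan fixes a different ratio: all non-adherent mononuclear cells to targets. The two move apart whenever the NK proportion differs between women or visits.

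The intervention includes exercise training, and the plan's own Background cites a training study in which the NK percentage rose. A rise in the intervention arm alone would be a post-allocation effect, so randomisation would not balance it. It could then be read as better NK function when each NK cell kills as before. A fall could equally hide a real gain. The same ambiguity would carry into the second secondary aim, which relates psychological status and stress hormones to immune indices. NK percentage and NK activity could also be taken as two independent immune findings when the second partly repeats the first.

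**Working it through.** **Step 1: the plan's own ratios.** Inputs from NK cell activity: 0.8 ml of effectors at 10^6 per ml, two-fold dilutions, 10^5 targets per tube.

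- Top tube: 0.8 × 10^6 = 8 × 10^5 effectors.
- Ratio = 8 × 10^5 / 2^i divided by 10^5, for i = 0 to 4: 8:1, 4:1, 2:1, 1:1, 0.5:1.
- Stated range: 80:1 to 5:1.

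The stated range is not reproduced; it is ten times too high for the stated cell numbers. It is obtained if the targets are 10^5 per ml, so that 100 μl holds 10^4: 8 × 10^5 / 10^4 = 80, then 40, 20, 10, 5. It would also follow from a starting effector concentration of 10^7 per ml: 8 × 10^6 / 10^5 = 80. A missing per ml on the targets looks the likelier slip, but the text does not settle it.

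**Step 2: what the ratio counts.** With f the NK fraction of the effectors, NK:target = (effector:target) × f. At a nominal 80:1, f = 10% gives 8 NK cells per target and f = 15% gives 12. The effector concentration is fixed, so the assay responds to the NK proportion and not to the NK count in blood. If all lymphocytes rose in parallel, f would not change.

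**Step 3: illustration of size.** The documents give no NK fraction, training-related shift, lysis level or killing curve. Everything in this step is assumed: lysis = 1 − exp(−k × NK:target), with k (killing per NK cell) unchanged. If f is multiplied by r, lysis L becomes 1 − (1 − L)^r. Starting from L = 20% and f = 10%:

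| NK fraction goes to | r | Lysis with k unchanged |
|---|---|---|
| 10% (no shift) | 1.0 | 20% |
| 12% | 1.2 | 1 − 0.8^1.2 = 23.5% |
| 15% | 1.5 | 1 − 0.8^1.5 = 28.4% |

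The last row equals log2(1.5) = 0.58 of a two-fold dilution step. This form depends only on r and the starting lysis, so the error found in step 1 does not alter it.

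**Step 4: range over the curve.** Taking the nominal ratios 80:1 to 5:1 and k from 0.05 to 0.2:

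- 10% to 12%: lysis rises by about 7% to 20% in relative terms, or 0.5 to 7 percentage points.
- 10% to 15%: lysis rises by about 14% to 49% in relative terms, or 1 to 15 percentage points.

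**Step 5: the two descriptions of the effectors.** Blood sampling has NK cells isolated; NK cell activity has monocyte-depleted mononuclear cells. These are different preparations. If NK cells really were isolated, the dependence on f would largely vanish. The detailed assay description contains no such step, so steps 2 to 4 rest on that description.

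**The case against.** Killing by mononuclear cells is a legitimate measure of total NK activity, and the plan says openly that this is what it measures. The NK proportion is a measured variable and can be shown next to it. The article is condensed, the assay is given only in brief with a reference to a published method, and scaling may be set out in a full protocol, a laboratory procedure or an analysis plan not shown. The background links to mood and survival do not specify killing per NK cell. No document figure shows how far the NK proportion might move. Nor does the outcome bear on the sample size.

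Most of this stands, and it limits the point. Several stronger readings are tempting but unsupported:

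- A reader might infer that the effectors are unfractionated. They are not; monocytes and macrophages are removed.
- A reader might infer that a change in NK numbers in blood drives the result. With a fixed effector concentration, only the proportion does.
- A reader might infer that a shift in proportion will be reported as a change in function. The text does not say so, and silence on scaling in an article is not a statement that none will be done.
- A reader might infer that the per-cell measure should replace total activity. That is a preference, and the per-cell measure has weaknesses of its own.

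The objection leaves two things untouched. The outcome as defined cannot by itself tell proportion from per-cell killing, while the hypothesis is worded as function. And the conflict over which cells are used, and the ratios that do not follow from the cell numbers, are faults in the text that an analysis plan would not cure.

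**Conclusion.** The point holds as a modest, inexpensive improvement to one biomarker outcome. As defined, NK activity mixes NK proportion with killing per NK cell, so a change in it does not on its own support a statement about NK cell function. The size in this trial is unknown. The 23.5% to 28% figures illustrate an assumed shift, starting lysis and curve, and the distortion is zero if the NK proportion does not move. The conclusion assumes that NK cells account for the killing of the target line and that the detailed assay description, not the Blood sampling sentence, is what will be done. Two errors are definite: the two sections disagree on the effector cells, and the stated ratios are ten-fold above what the stated cell numbers give. The sample size is set on body weight, so neither that outcome nor the power is affected.

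**What to change.** 1. Correct the cell numbers or the ratios in NK cell activity so that they agree. This comes first, because any NK:target ratio is built on them.
2. Reconcile Blood sampling with NK cell activity on whether NK cells or monocyte-depleted mononuclear cells are the effectors.
3. Keep killing per mononuclear cell, labelled as total NK activity. Add a prespecified analysis of killing per NK cell: lysis over the full dilution series against NK:target = effector:target × NK proportion, with the proportion taken from Lymphocyte phenotyping.
4. State that a change will be attributed to NK function only if the per-cell analysis supports it, and report NK proportion beside both measures.

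The cost is a text correction and a calculation on data already planned; no new sample or visit is needed. There is a statistical price. The whole-blood NK proportion only approximates the fraction in the tube after Ficoll separation and adherence, so selective cell loss could bias the per-cell measure. Error in the proportion also enters that measure and can induce a negative association between NK percentage and per-cell killing. For these reasons the per-cell analysis belongs beside total activity and not in its place.

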##### Lymphocyte proliferation assays

Peripheral blood lymphocyte proliferative responses to recall antigen (purified protein derivative, PPD) will be determined. Peripheral blood mononuclear cells will be isolated as described above and 10^5 ^cells incubated for 7 days (37°C, 5% CO_2_) with an appropriate concentration of PPD (~1 μg/ml) in 96-well microtitre plates. Antigen non-specific proliferation will be determined by incubating cells with plate-bound anti-CD3 mAb and soluble anti-CD28 mAb (both 10 μg/ml) (BD Biosciences). For both assays, proliferation will be determined by preincubating cells with 5,6-carboxyfluorescein diacetate succimidyl ester (CFSE)(Molecular Probes) and subsequent measurement of the amount of dye per cell by flow cytometry [102].

### Data Analysis

A mixed factorial ANOVA will be used to assess (i) changes from baseline on all outcome measures following the intervention within patient groups, and (ii) differences in outcome measures between patients in the lifestyle intervention and control groups post intervention. Pearson product moment correlation coefficients (r) will be calculated to determine bivariate relationships among changes in the variables. Statistical significance will be set at *p *< 0.05. All data will be analysed using the SPSS statistical package (SPSS UK Ltd, Woking, U.K.).

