### Details of power calculations and sample size

Body weight was chosen as the primary outcome variable for calculation of sample size. Utter *et al*. [88] reported a 8.1 kg reduction in body weight in obese women following a 12 week lifestyle intervention, incorporating moderate dietary energy restriction in conjunction with exercise. Body weight changed from a baseline ± SD level of 89.9 ± 11.7 to 81.8 ± 10.8 kg following the intervention. This amount of weight loss is associated with improved physical and psychological health in obese women [41,90]. On the basis of these data, and taking into account an expected patient drop-out of up to 10% (based on the drop-out rate in our ongoing trial with breast cancer survivors [91]), recruitment of 50 patients for each group will give us 90% power to detect a difference in body weight of 8 kg at the α level of 0.05.

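### Neither contrast named in the Data Analysis section is a baseline-adjusted comparison of the randomised groups, so the test of the treatment effect on body weight is left open and may lose precision

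*Protocol article*

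**What the plan says.** The Data Analysis section of the protocol article assigns the model two tasks. The first is introduced with "A mixed factorial ANOVA will be used to assess (i) changes from baseline on all outcome measures following the intervention within patient groups". The second is to assess "differences in outcome measures between patients in the lifestyle intervention and control groups post intervention". It names no baseline covariate and no between-group comparison of change.

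Three other sections bear on this:

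- **Details of power calculations and sample size.** Body weight is the outcome on which the trial is sized. The source data are "Body weight changed from a baseline ± SD level of 89.9 ± 11.7 to 81.8 ± 10.8 kg following the intervention". The claim is that "recruitment of 50 patients for each group will give us 90% power"; the target is a between-group gap of 8 kg, tested at a significance level of 0.05, with up to 10% drop-out allowed for.
- **Randomisation.** Minimisation covers chemotherapy and hormone therapy, not weight or BMI. Outcomes are measured in the week before the intervention, at 12 weeks and in the week after it (called week 24 below).
- **Primary outcome measure.** The primary outcome is body weight and body composition, so baseline weight will be on file for both groups.

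**The concern.** The primary aims concern the effect of the intervention, which in a randomised trial is a difference between groups. As worded, neither contrast is a baseline-adjusted version of that difference.

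- **Contrast (i)**, "changes from baseline on all outcome measures following the intervention within patient groups", describes each arm separately. A change within an arm mixes any treatment effect with time trends and regression to the mean. A significant change in one arm and a non-significant change in the other does not show that the arms differ.
- **Contrast (ii)** is a randomised comparison. Read literally, though, it uses final values only and ignores a strong predictor of final weight.

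The model also contains a group-by-time interaction, which does use baseline. The text does not single it out as the treatment test. If the 12-week measurement is a level of the time factor, the omnibus interaction has two degrees of freedom and does not isolate week 24.

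At stake is the precision of the main result, and a realised estimate that a chance baseline difference can move towards or away from an effect. The same wording covers every other outcome, and the article gives no power calculation for those.

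**Working it through.** **Inputs.** From the sample-size section: difference 8 kg, SD 11.7 kg at baseline and 10.8 kg afterwards, α 0.05 (taken as two-sided), power 90%, drop-out 10%, 50 per group. The correlation r between baseline and week-24 values is not in the article. It is assumed to lie between 0.5 and 0.95.

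**1. The plan's own figure.** n per arm = 2(1.960 + 1.282)² × 11.7² / 8² = 44.9, so 45. Then 45 / 0.90 = 50. The stated size reproduces. Power at 45 per arm is 90.0% by the normal formula and 89.4% by the noncentral t.

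**2. Chance baseline imbalance.** The SE of the baseline difference is 11.7 × √(2/50) = 2.34 kg for all randomised patients and 11.7 × √(2/45) = 2.47 kg for completers. The shift carried into the final-value difference is the imbalance times the slope r × 10.8/11.7. At 45 per arm:

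| assumed r | 1-SE imbalance | 2-SE imbalance |
|---|---|---|
| 0.5 | 1.1 kg | 2.3 kg |
| 0.7 | 1.6 kg | 3.2 kg |
| 0.8 | 1.8 kg | 3.6 kg |
| 0.9 | 2.1 kg | 4.1 kg |
| 0.95 | 2.2 kg | 4.3 kg |

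**3. Precision under three readings.** Settings are 45 per arm, a common SD of 11.7 kg, two-sided 0.05, 90% power and the t distribution.

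- Final values only: SD 11.7.
- Change score (the interaction with two time points): SD = 11.7 × √(2(1 − r)).
- ANCOVA on baseline: SD = 11.7 × √(1 − r²).

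Detectable differences, with 95% CI half-widths in brackets:

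| assumed r | final values only | ANCOVA | SD, change score | SD, ANCOVA | ANCOVA SD lower than change score by |
|---|---|---|---|---|---|
| 0.7 | 8.1 kg (±4.9) | 5.8 kg (±3.5) | 9.06 | 8.36 | 8% |
| 0.8 | 8.1 kg (±4.9) | 4.9 kg (±2.9) | 7.40 | 7.02 | 5% |
| 0.9 | 8.1 kg (±4.9) | 3.5 kg (±2.1) | 5.23 | 5.10 | 3% |
| 0.95 | 8.1 kg (±4.9) | 2.5 kg (±1.5) | 3.70 | 3.65 | 1% |

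The normal formula gives 8.0 kg in place of 8.1 kg.

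**4. Outcomes with lower correlation.** At r = 0.5, plausible for questionnaires but also assumed, the change-score variance is 2(1 − 0.5) = 1.0 times that of final values, so a change score gains nothing. The ANCOVA variance is 1 − 0.5² = 0.75 times, which is 25% lower than either.

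**The case against.** The strongest reply is that the plan names a mixed factorial ANOVA, and that model contains a group-by-time interaction. With two time points the interaction is a comparison of change scores, a valid randomised comparison that uses baseline. This stands. The weakness is in the contrasts as worded, not in the model family, and the fall from 8.1 kg to between 5.8 and 2.5 kg applies only if contrast (ii) is a final-value test. For weight, ANCOVA improves little on a change score. The reply does not settle the matter, because the text never says the interaction is the treatment test.

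It can also be said that a journal article leaves model detail to a fuller document. That is fair for covariate lists and model terms. Here, however, the article itself states which contrasts will be assessed, and those can be judged as written.

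A reader might infer more than the article supports:

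- **That the final-value comparison is biased or invalid.** It is not. Randomisation makes it unbiased on average, and its 5% type I error already allows for chance imbalance. The 90% power for 8 kg also stands.
- **That a baseline imbalance passes into the result in full.** It is scaled down by the slope in step 2.
- **That the sample size proves an unadjusted analysis.** Sizing on the raw SD fits one, but the article quotes no SD of change, and a raw SD can be used as a cautious choice for an adjusted analysis.
- **That benefit will be claimed from one arm's within-group p-value.** The article does not say so, and it lists a between-group comparison alongside.

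**Conclusion.** The point holds in limited form. The Data Analysis section names no between-group contrast that uses baseline, although baseline weight is measured in everyone and minimisation does not balance it. The cost is precision and a chance shift in the realised estimate, not validity or the planned power.

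The size depends on which test is meant. If it is final values only, a baseline covariate lowers the detectable weight difference by roughly 29% to 69% over the assumed r of 0.7 to 0.95 (1 − 5.8/8.1 = 0.28 from rounded figures, or 1 − √(1 − r²) = 0.29 to 0.69 on the SD). If it is the interaction, the further gain for weight is 8% of the SD or less over that range, and the larger benefit falls on outcomes with weaker correlation. All these gains rest on assumed correlations, a common SD of 11.7 kg and 45 completers per arm. The point is worth settling before analysis and does not call the design into question.

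**What to change.** Replace the two contrasts in the Data Analysis section with wording such as:

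*The treatment effect is the between-group difference in week-24 body weight, estimated by ANCOVA with baseline weight as covariate (or by the equivalent linear mixed model with a week-24 contrast), and reported with its 95% confidence interval. Other outcomes are analysed in the same way, each with its own baseline value. Within-group changes are presented descriptively and are not taken as evidence of the intervention's effect.*

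If the authors prefer to keep the repeated-measures ANOVA, an explicit group-by-time contrast between baseline and week 24, named as the treatment test, would also be a valid comparison that uses baseline. It would be less efficient for outcomes with weaker correlation.

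The cost is one paragraph of text. It needs no new measurements, no additional patients and no change to the stated sample size, and the software already named can be used.

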### Randomisation

The minimisation technique [89] will be used to allocate the patients into one of two groups (i) lifestyle intervention group, incorporating moderate dietary energy restriction of 600 kcal per day in conjunction with aerobic exercise training on 3–5 days per week, or (ii) normal care control group. Minimisation will be used to balance the potentially confounding variables of chemotherapy and treatment with Tamoxifen, aromatase inhibitors or no hormone therapy across the groups. Randomisation will be performed by an independent researcher at the Clinical Trials Research Unit, University of Leeds. The intervention will last for 24 weeks, with outcome measures being assessed in the week before and the week after the intervention period and at the mid-intervention time point of 12 weeks. Patients would be recruited over 16 months, ensuring completion of the trial by 22 months and reporting of the data by 24 months.

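### The ANOVA named for all outcomes does not include the two minimisation factors, so the post-intervention between-arm test is conservative to the extent that those factors predict the outcome

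*Protocol article*

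**What the plan says.** Under Randomisation, the protocol article states: "The minimisation technique [89] will be used to allocate the patients into one of two groups". It gives the purpose and the factors: "Minimisation will be used to balance the potentially confounding variables of chemotherapy and treatment with Tamoxifen, aromatase inhibitors or no hormone therapy across the groups".

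Under Data Analysis, a single mixed factorial ANOVA is named for every outcome. It serves two purposes. One is change over time inside each arm. The other is the contrast between arms at the end of treatment, worded as "differences in outcome measures between patients in the lifestyle intervention and control groups post intervention". That section goes on to correlations, the significance level and the software. It mentions no covariate and no between-subject factor other than group.

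The sample size is an unadjusted two-group calculation on weight: "Body weight was chosen as the primary outcome variable for calculation of sample size". With α set to 0.05, the claim made for it is: "recruitment of 50 patients for each group will give us 90% power to detect a difference in body weight of 8 kg at the α". The article does not say how strongly chemotherapy or hormone therapy predicts weight, mood or any biomarker.

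**The concern.** The sponsor considered these two factors important enough to constrain allocation, but the analysis it names makes no use of them. Forced balance means that the factors can hardly contribute to the difference between arms. A model without them still counts the variance they explain as residual error. The estimated standard error then exceeds the true sampling error of the difference, intervals are wider than they need be, and the test rejects less often than its nominal level.

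What is at stake is efficiency. It matters most where hormone therapy or earlier chemotherapy could plausibly explain a real share of the variance. Estradiol, estrone and estrone sulphate are the obvious case, because women on endocrine treatment are eligible. Biomarkers are part of the second primary aim, yet power is stated for weight alone.

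**Working it through.** **Inputs from the article.** 50 patients per group, drop-out up to 10%, difference 8 kg, power 90%, α 0.05 (sidedness not stated; two-sided reproduces the figure). SDs come from the cited weight-loss study: "Body weight changed from a baseline ± SD level of 89.9 ± 11.7 to 81.8 ± 10.8 kg following the intervention".

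**Assumed input.** R², the share of outcome variance explained by the minimisation factors. The documents give none; the range taken is 0 to 0.30.

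**Step 1: reproduce the sample size.** n per group = 2(1.960 + 1.282)² × 11.7² / 8² = 45 after rounding up. Then 45 / (1 − 0.10) = 50, as stated. Power at 45 per group is 0.900 (0.894 by noncentral t). With SD 10.8, power at 45 per group is 0.940. The stated figure therefore holds with no covariate in the model.

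**Step 2: true type I error of the unadjusted post-intervention test.** Under complete balance the true standard error is √(1 − R²) times the estimated one, so the actual level is 2Φ(−1.96/√(1 − R²)).

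**Step 3: power.** Let λ be the nominal noncentrality, that is, the effect divided by the unadjusted standard error. For nominal 80% power, λ = 1.960 + 0.842 = 2.802. For weight, the unadjusted standard error is 11.7 × √(2/45) = 2.47 kg, and λ = 8/2.467 = 3.24.

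- Unadjusted under forced balance: 1 − Φ((1.96 − λ)/√(1 − R²))
- Adjusted: Φ(λ/√(1 − R²) − 1.96)

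| R² | Actual level, unadjusted | Nominal 80% outcome: unadjusted → adjusted | Weight, SD 11.7: unadjusted → adjusted | Adjusted SE, weight (kg) |
|---|---|---|---|---|
| 0.05 | 4.4% | 0.806 → 0.820 | 0.906 → 0.914 | 2.40 |
| 0.10 | 3.9% | 0.813 → 0.840 | 0.912 → 0.928 | 2.34 |
| 0.20 | 2.8% | 0.827 → 0.879 | 0.924 → 0.952 | 2.21 |
| 0.30 | 1.9% | 0.843 → 0.918 | 0.937 → 0.972 | 2.06 |

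**Step 4: does minimisation balance well enough for these formulas?** A simulation of 90 patients allocated by minimisation (80% biased coin or deterministic) gave null rejection without adjustment of 4.9–5.0%, 4.0% and 2.8–3.0% at R² 0, 0.10 and 0.20. With adjustment it was 4.9–5.0% throughout. At R² 0, power for 8 kg was 89% either way, so adjusting for useless factors had no visible cost.

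**Step 5: which ANOVA term is affected?** A second simulation used 96 patients in six equal factor cells split evenly between arms, an assumed pre/post correlation of 0.8 and 3,000 runs. The Monte Carlo error on a 5% rate is √(0.05 × 0.95/3000), about 0.4 points. The factors' R² was 0.10, applied either to level or to change.

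| Factors shift | Comparison | SE unadjusted / adjusted | Null rejection unadjusted / adjusted |
|---|---|---|---|
| level only | change (group by time) | 0.1286 / 0.1286 | 5.1% / 5.1% |
| level only | post-intervention | 0.215 / 0.203 | 4.0% / 4.9% |
| change | change (group by time) | 0.1355 / 0.1285 | 3.4% / 4.5% |

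With an effect of 0.36 (within-cell SD = 1), power for change was 74% unadjusted and 78% adjusted when the factors predicted change. It was 79% either way when they shifted level only.

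**The case against.** The strongest reply is that a short paragraph in a journal article names a family of analysis and not a full list of model terms. Covariates are often left to a statistical analysis plan, which is not shown here, and nothing says the factors will be excluded. That is fair as far as it goes: a fuller document may already include them. But the section fixes a method for all outcomes and spells out its two comparisons, and the point is that a better model than the one described is available at almost no cost.

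The second reply is that stable differences between patients cancel in the group-by-time term. This stands. If chemotherapy and hormone therapy only shift a patient's level, that term loses nothing. The loss then falls on the post-intervention comparison, which the article also commits to.

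The third is that no R² is documented. This also stands. Naming the factors as possible confounders gives no variance share, so every size above is conditional.

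A reader might infer that real effects on weight, mood and biomarkers will be missed. The documents do not support that. For weight, unadjusted power is 0.906 to 0.937 over R² 0.05 to 0.30, never below the stated 90%, and adjustment adds only 0.8 to 3.5 points. For mood and biomarkers, no power and no R² are given from which such a conclusion could be drawn.

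**Conclusion.** The point holds as a conditional loss of efficiency. The analysis described does not use the factors that governed allocation. If they are prognostic, the post-intervention between-arm test is conservative: about 3.9%, 2.8% and 1.9% in place of 5% at R² 0.10, 0.20 and 0.30. For an outcome with nominal 80% power, the power forgone is 2.7 points at R² 0.10 (0.840 − 0.813) and 7.5 points at 0.30 (0.918 − 0.843), which is small to moderate. Group-by-time is affected only where the factors predict change.

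These sizes rest on the assumed R² range and on near-complete balance among the patients analysed. If drop-out disturbs that balance, the actual level moves back towards 5%.

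It would be wrong to read this as an invalid analysis. The treatment estimate is not biased, false positives are not inflated, and the sample size for weight reproduces and is adequate without adjustment. The benefit lies mainly with biomarkers such as estrogens, where hormone therapy may explain more of the variance, though the documents do not quantify this.

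**What to change.** In Data Analysis, add one sentence: chemotherapy (yes/no) and hormone therapy (Tamoxifen, aromatase inhibitor or none), coded as recorded for minimisation, enter the between-arm models as between-subject terms, and the treatment effect and its interval are taken from those models. If a fuller analysis plan already says this, a cross-reference is enough.

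The cost is 3 degrees of freedom (1 for chemotherapy, 2 for hormone therapy). No new data, visits or patients are needed, since both factors are recorded at allocation. The sample size can stay as it is.
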